## Abstract

**Background:**

Bariatric surgery is an effective approach to weight loss and long-term comorbidity resolution. Although recommended in several guidelines, supervised exercise has not been systematically prescribed after bariatric surgery. The aim of this study is to determine the effects of two types of exercise, moderate-intensity continuous training (MICT) and high-intensity interval training (HIIT), on body composition, cardiopulmonary function, and perceived quality of life in bariatric surgery patients.

**Methods:**

This randomized controlled exploratory pilot trial will include 75 adults of both sexes scheduled for bariatric surgery. They will be randomly assigned to one of three groups: (1) MICT, (2) HIIT, or (3) a control group. The intervention will occur 2 days a week for 4 months. Outcomes will be assessed at four points: (1) 1 week before surgery, (2) 21 days after surgery (baseline before the exercise program), (3) 8 weeks after beginning the exercise program, and (4) 1 week after the end of intervention. Primary outcomes will include body composition, heart rate variability, and 6-min walk test and quality of life scores. Secondary outcomes will be maximal respiratory pressure, flowmeter, hand dynamometry, and 30-s sit-to-stand test results.

**Discussion:**

Both exercise protocols in this study were developed according to evidence-based practice. It is expected that, after 16 weeks of intervention, body composition (measured by electrical bioimpedance), cardiopulmonary function (measured by heart rate variability, maximal inspiratory pressure, maximal expiratory pressure, peak expiratory flow, handgrip strength, and the 6-min walk test), and perceived quality of life (measured by the Moorehead-Ardelt quality of life questionnaire II and bariatric analysis and reporting outcome system scores) will improve, especially in the HIIT group.

**Trial registration:**

ClinicalTrials.gov NCT04235842. Registered on 22 January 2020.

## Introduction

### Background and rationale {6a}

Obesity is an abnormal state of health characterized by excess body fat due mainly to caloric intake and expenditure imbalance [1]. The daily energy consumption of this population is estimated at approximately 3000 Kcal/day, far above the requirements of sedentary individuals [2].

In its latest National Health Survey (2017), Chile was found to have a high risk of non-communicable diseases and a few protective factors. A total of 10,301,529 Chileans (58.6% of the population) has some degree of excess weight, of whom 39.8% are overweight, 31.2% are obese, and 3.2% are morbidly obese.

Studies have shown [3–5] that obesity leads to a state of chronic inflammation and oxidative stress, which is related to numerous chronic diseases such as cardiovascular and respiratory diseases [6, 7]. Obese people also suffer from social pressure, leading to impaired social interaction, body image rejection and low self-esteem, which compromises their psychological health, well-being and, thus, negatively impacts their quality of life [8, 9].

When morbidly obese patients do not respond to the usual obesity treatments, such as exercise, dieting, and pharmacological treatment, they become candidates for restrictive and/or malabsorptive bariatric surgery [10, 11]. Currently, four procedure types exist: adjustable gastric band, Roux-en-Y gastric bypass, vertical sleeve gastrectomy, and bilio-pancreatic bypass [12, 13].

Patients usually experience significant weight loss in the first postoperative year (56 to 85% of their excess weight), of which about 70% is fat mass and 30% lean mass [14]. Some studies have shown that bariatric surgery results not only in weight loss and comorbidity changes, but also in complications such as severe anemia, osteopenia, dehydration, constipation, intestinal obstruction, vitamin and mineral deficiency, fatigue, and posture changes [15, 16]. Preventing such complications is crucial for bariatric surgery patients, especially through non-pharmacological means.

Thus, exercise could be a relevant solution since it maintains muscle mass, generates tension and load on the bones, activates the metabolism, red blood cell production and intestinal peristalsis, improves cardiopulmonary function and general functionality, contributes to bone mineralization, and helps maintain independence [17]. Indeed, several studies have shown the benefits of regular exercise before and after bariatric surgery [18–20].

Among bariatric surgery patients, moderate-intensity continuous training (MICT) effectively decreases postoperative lean mass loss and increases fat mass loss, controls glucose homeostasis, and improves cardiovascular capacity [20–22]. High-intensity interval training (HIIT) has recently been proposed as an alternative to MICT and is well tolerated by overweight and insulin-resistant individuals [23, 24]. The HIIT method has proven effective in improving cardiorespiratory fitness, maximal oxygen uptake (VO_2_max), and insulin sensitivity in healthy subjects [25–27]. In addition, it has been described as more motivating than MICT due to a greater feeling of fatigue and its shorter sessions [28]. However, to our knowledge, no studies have compared the effectiveness of MICT and HIIT in postoperative bariatric surgery patients.

Although participation in regular physical activity programs is a standard recommendation after bariatric surgery in Chile, supervised exercise is not currently recommended or prescribed. Therefore, clarifying the effects of MICT and HIIT on body composition, cardiopulmonary function, and quality of life after bariatric surgery is relevant, especially in our local context.

### Objectives {7}

This study will aim to determine the effect of MICT and HIIT programs on body composition, cardiopulmonary function, and perceived quality of life in bariatric surgery patients. We will also compare the effects of supervised exercise programs with those of standard follow-up. We hypothesized that both exercise programs would lead to greater improvement in the assessed outcomes than standard recommendations. Moreover, we expect the HIIT protocol to result in greater gains than MICT.

### Trial design {8}

This protocol is a randomized pilot exploratory study, single-blind, three-arm, parallel-group study. Participants will be randomly assigned to one of the three groups: (1) a control group (CG), (2) a moderate-intensity continuous exercise training group (MICT-G), or (3) a high-intensity interval exercise training group (HIIT-G).

## Methods: participants, interventions, and outcomes

### Study setting {9}

The study will be carried out at the Department of Physical Medicine and Rehabilitation Service in the San Juan de Dios Hospital, a public hospital in the city of Curicó, located at [name], in the Maule region, Chile. All procedures will be conducted by at least two experienced physiotherapists and the department is strategically located to ensure that any medical emergencies can be promptly cared for. All procedures will be performed in a room with controlled temperature (22–24 °C) and air humidity (40–60%).

### Eligibility criteria {10}

#### Inclusion criteria

Participants of either sex will be considered eligible if they are between 18 and 65 years old, have undergone bariatric surgery at the above-mentioned hospital, have been cleared for exercise, are in the final phase of operative wound healing, have been administered antithrombotics after surgery, and have no plans to change their residence in the year after surgery.

#### Exclusion criteria

Participants with immediate postoperative complications (anastomosis or wound dehiscence) or decompensated comorbidities, who are on dialysis, or who suffer from a neuromotor disease will be excluded.

### Who will take informed consent? {26a}

After receiving a list of patients scheduled for bariatric surgery from a staff member of Bariatric Surgery Service of the hospital, [name] will telephone each patient, invite them to participate, and make an individual appointment. In this, the objective of the study, inclusion and exclusion criteria, participation, risks, benefits, and ethical implications will be explained. In the case that the potential participant wants to participate in the research, the informed consent will be signed in 3 copies: one for the participants, one for the researcher, and one for de clinical record from the hospital.

### Additional consent provisions for collection and use of participant data and biological specimens {26b}

Not applicable, this trial does not have biological specimens.

## Interventions

### Explanation for the choice of comparators {6b}

Participants will be randomly assigned to one of the three groups: (1) a control group (CG) that will receive standardized recommendations, (2) a moderate-intensity continuous exercise training group (MICT-G), or (3) a high-intensity interval exercise training group (HIIT-G).

### Intervention description {11a}

Participants allocated to the MICT and HIIT groups will perform two weekly sessions of supervised exercise for 16 weeks. Sessions will be divided into a 3-week adaptation period and 13 weeks of formal training. All sessions will consist of:
Joint mobility (3 min): head and neck, shoulder, elbow, wrist, hip, knee, ankle, and trunk.Warm-up (7 min): treadmill walking at 1–2 km/h.Aerobic component:
MICT group: 15 min on a cycle ergometer at moderate intensity (40–60% of heart rate reserve) or at a perceived exertion rating of 5–6 out of 10.HIIT group: 8 min on a cycle ergometer, including a 60-s sprint at 90% maximal heart rate followed by a 60-s rest until four sets are completed.Strength training: 15 min of exercise in the large muscle groups with weight machines or dumbbells, including 1–2 sets of 8–10 repetitions at 50–60% of one-repetition maximum strength (1RM).Cool-down (5 min): proprioceptive neuromuscular facilitation exercises for abdominal muscles and the pelvic floor will be performed on a mat. Stretching exercises for arm, leg, and trunk muscles will be performed in three 30-s sets. Hemodynamic variables will be checked to ensure that blood pressure and heart rate values return to baseline.

#### Exercise progression

Beginning with the fourth week, the aerobic load in the MICT group will be adjusted to 60% of the heart rate reserve and the duration will be adjusted to 30 min. In the HIIT group, the number of sets will be increased to 1 by week until 10 sprints. Strengthening exercises will be performed in 3 sets of 10–12 repetitions, with intensities between 60 and 70% 1RM. The 1RM value will be assessed at baseline and week 8.

During both training programs, heart rate, blood pressure, oxygen saturation, and perceived exertion will be evaluated with the Borg CR-10 scale.

Participants allocated to the CG will be following the indications of regular physical activity practice according to WHO (at least 150 min per week of moderate physical activity or at least 75 min of intense physical activity), which will be explained by [name]. The protocol followed by all patients operated of bariatric surgery at the San Juan de Dios hospital is to receive these indications.

### Criteria for discontinuing or modifying allocated interventions {11b}

Will be criteria for discontinuing: participant request, severe alteration of hemodynamic parameters during the training, participants who attend less than 85% of the training sessions, participants who were absent on evaluation days, and participants from the training group who engage other regular physical exercise.

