### Outcomes {12}

Outcomes will be assessed at four time points: (1) 1 week before surgery, (2) 21 days after surgery (baseline before starting the exercise program), (3) 8 weeks after the beginning of the exercise program, and (4) 1 week after the end of intervention.

Primary outcomes will be (1) body composition, (2) heart rate variability, (3) 6-min walk test results, and (4) perceived quality of life. Secondary outcomes include the results for (1) maximal respiratory pressure, (2) flowmeter, (3) hand dynamometry, (4) the 30-s sit-to-stand test, and (5) the basal metabolic rate.

Data collection will include sex, age, place of residence, marital status, education level, and physical activity level according to the International Physical Activity Questionnaire [29].

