### Methods in analysis to handle protocol non-adherence and any statistical methods to handle missing data {20c}

Per-protocol and intention-to-treat analysis will be performed in order to account for the possible dropouts during the study. In the per-protocol analysis, we will include only the participants who attended at least 85% of the sessions and underwent the baseline and post intervention outcome assessments. For the intention-to-treat analysis, we will consider all the participants who underwent the baseline assessments and after being assigned to one of the study groups took part in at least one session. Missing data will be handled by multiple imputation method. Five imputed data sets will be obtained by multiple linear regression models for each variable. The final imputed value will be the arithmetic mean of the 5 data values created.

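### Section 11b makes missed evaluations, attendance below 85% and outside exercise grounds for discontinuing; if that means leaving the study, outcomes needed for the intention-to-treat analysis are lost, partly in the exercise arms only

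*Protocol article*

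**What the plan says.** Section {11b} of the protocol article gives one undivided list of five criteria for discontinuing. Two are participant request and severe haemodynamic alteration during training. Two more concern attendance and assessment: "participants who attend less than 85% of the training sessions, participants who were absent on evaluation days". The fifth applies to the exercise arms alone and covers "participants from the training group who engage other regular physical exercise".

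Supervised sessions exist only in the MICT and HIIT arms, whose participants "will perform two weekly sessions of supervised exercise for 16 weeks" ({11a}). Controls are advised to be physically active under the WHO recommendation ({11a}, exercise progression). After the pre-surgery and baseline assessments, outcomes are measured at "3) 8 weeks after the beginning of the exercise program, and (4) 1 week after the end of intervention" ({12}).

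Section {20c} sets out two analyses. For the first: "In the per-protocol analysis, we will include only the participants who attended at least 85% of the sessions", and these participants must also have baseline and post-intervention assessments. For the second: "For the intention-to-treat analysis, we will consider all the participants who underwent the baseline assessments", provided they were assigned and took part in at least one session. It adds: "Missing data will be handled by multiple imputation method".

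Section {18b} provides reminder messages and a telephone call asking why a session or evaluation was missed. No section says whether a discontinued participant is still assessed.

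**The concern.** Request and haemodynamic alteration are sound reasons to stop training. The other three items are adherence or follow-up events. Absence from an evaluation concerns data collection, and for a control it can hardly mean anything but leaving the study. Someone who missed only the week-8 visit would then lose the final visit too.

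If the attendance and outside-exercise items are applied in the same way, outcome collection stops because of behaviour after randomisation, and only in the exercise arms. The comparison at stake is the one in {7}: "We will also compare the effects of supervised exercise programs with those of standard follow-up". Randomisation does not protect it against loss of this kind. Section {20c} keeps these participants in the intention-to-treat set, so one section would create the gaps that another has to fill by imputation.

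**Working it through.** **Inputs from the protocol.** Two sessions a week for 16 weeks ({11a}); 85% threshold ({11b}, {20c}); effect size 1.01, 80% power, 5% significance, 17 per group raised to 25 ({14}).

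**Assumptions.** The protocol gives no attendance or missed-visit rates. I assume mean attendance of 85–95%; sessions that are independent or correlated within person (beta-binomial, ICC 0.05 to 0.3); 5–15% missing week 8; and a difference of 0.25–1.0 SD between participants kept and lost.

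**1. The plan's own figure.** A two-sample t-test, two-sided 5%, d = 1.01, 80% power needs 16.4, rounded up to 17 per group. This reproduces {14}. Going from 17 to 25 allows for 8 losses per arm (8/25 = 32%).

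**2. Where the attendance rule bites.** 2 × 16 = 32 sessions and 0.85 × 32 = 27.2, so 28 are needed. Four absences are tolerated; the fifth breaks the rule.

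**3. Share of an exercise arm meeting the rule**, P(X ≤ 27 of 32):

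| Mean attendance | Independent | ICC 0.05 | 0.1 | 0.2 | 0.3 | Of 25 |
|---|---|---|---|---|---|---|
| 95% | 0.020 | 0.088 | 0.112 | 0.122 | 0.116 | 1–3 |
| 90% | 0.211 | 0.264 | 0.268 | 0.254 | 0.233 | 5–7 |
| 85% | 0.536 | 0.473 | 0.438 | 0.387 | 0.346 | 9–13 |

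For controls the share is zero. The same holds for the outside-exercise rule, and the haemodynamic criterion also presupposes training. So three of the five criteria can be met only in the exercise arms.

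**4. Power if all of these were lost** (noncentral t, d = 1.01, two-sided 5%, complete cases):

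| Left in each exercise arm | Versus 25 controls | HIIT versus MICT, same d |
|---|---|---|
| 25 | 0.938 | 0.938 |
| 20 | 0.908 | 0.875 |
| 18 | 0.891 | 0.837 |
| 16 | 0.868 | 0.789 |
| 12 | 0.799 | 0.657 |

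The rows with 20 and 18 correspond to 90% attendance, and those with 16 and 12 to 85%. Taking d = 1.01 for HIIT versus MICT is generous, because {14} took it from a comparison of MICT with control.

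**5. Possible bias.** Shift of the observed arm mean = share lost × (mean of kept − mean of lost). At 90% attendance this runs from 0.21 × 0.25 = 0.05 SD to 0.27 × 1.0 = 0.27 SD, before any correction by imputation. The sign is open: the attendance rule removes poor attenders, while the outside-exercise rule may remove the most active.

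**6. Missed-evaluation rule, all arms.** If 5–15% miss week 8, then 25 × 0.05 = 1.3 to 25 × 0.15 = 3.8, so about 1–4 per arm would also lose the final visit.

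**The case against.** The strongest reply is that the text never says a discontinued participant leaves the study. The heading of {11b} concerns the allocated intervention, and {20c} lists attendance and completed assessments as separate per-protocol conditions, which suggests that some participants below 85% are expected to have final outcomes. A journal article may also leave follow-up after discontinuation to the full protocol. This stands as far as the attendance item goes: a reading in which only training stops is open. It does not rescue the missed-evaluation item, which makes little sense as a reason to stop training and stands in the same list without distinction. Nor is the point merely one of omitted detail, since the article itself fixes these criteria.

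The size can also be challenged. Attendance is assumed, and the power figures describe complete cases rather than the planned imputed analysis. The rule also tends to bite late: at 90% attendance, the fifth absence falls after session 16 (about week 8) in 92% of those who break the rule with independent sessions, 68% at ICC 0.1 and 44% at ICC 0.3. At 85% attendance the figures are 85%, 61% and 41%. Many would therefore have week-8 data and lose only the final visit. All of this is fair. The 5–7 losses at 90% attendance also fit within the allowance of 8.

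Finally, controls have no sessions to miss, so some asymmetry is built into the design. That explains the asymmetry but does not justify ending outcome collection because of it. Imputation may recover part of the loss, but it relies on a model where a measurement was available.

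**Conclusion.** The concern holds, in conditional form, and should be fixed. As written, {11b} makes a missed evaluation a reason to discontinue and leaves it open whether poor attendance and outside exercise also end assessment. If they do, the trial creates avoidable missing outcomes, partly specific to the exercise arms, in its comparison with standard follow-up.

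The threshold of five absences out of 32 follows from the protocol; every other size rests on the stated assumptions. Losses in an exercise arm could be negligible (2% at 95% attendance, independent sessions) or about half (54% at 85%). Power against control stays at about 80% or more throughout. Only HIIT versus MICT loses material power, down to 66–79% at 85% attendance. The main issue is bias of unknown direction and needless reliance on imputation. Confidence is medium, because the milder reading may be what the investigators intend.

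**What to change.** Reword {11b} in four respects:

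- State that the criteria end or modify training only.
- Invite every randomised participant who has not withdrawn consent to the week-8 and final assessments.
- Remove the missed evaluation from the list and treat it as a missing value at that visit.
- Use 85% attendance, and outside exercise if wanted, only to define the per-protocol set in {20c}.

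The cost is small. The visits are already scheduled in {12}, the call after a missed session or evaluation is already planned in {18b}, and no change in sample size follows. The downside is some effort to bring poor attenders back for assessment. If the investigators already mean that only training stops, this merely puts the intention in writing.

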### Strategies to improve adherence to interventions {11c}

Not applicable, this trial does not have strategies to improve adherence.

### Relevant concomitant care permitted or prohibited during the trial {11d}

Not applicable, this trial does not have concomitant care permitted or prohibited.

### Provisions for post-trial care {30}

Once the study is completed, the CG and group with less effect of the study will be invited to carry out the training that has obtained the best effect.

### Outcomes {12}

Outcomes will be assessed at four time points: (1) 1 week before surgery, (2) 21 days after surgery (baseline before starting the exercise program), (3) 8 weeks after the beginning of the exercise program, and (4) 1 week after the end of intervention.

Primary outcomes will be (1) body composition, (2) heart rate variability, (3) 6-min walk test results, and (4) perceived quality of life. Secondary outcomes include the results for (1) maximal respiratory pressure, (2) flowmeter, (3) hand dynamometry, (4) the 30-s sit-to-stand test, and (5) the basal metabolic rate.

Data collection will include sex, age, place of residence, marital status, education level, and physical activity level according to the International Physical Activity Questionnaire [29].

#### Body composition

Body composition will be measured with tetrapolar bioelectrical impedance, (INBODY 270, Inbody Co. Ltd., Korea). The body fat percentage, muscle and bone mass, and basal metabolic rate will be evaluated.

#### Heart rate variability

R-R intervals will be recorded with a Polar V800 heart rate monitor (Polar, Oi, Finland); a sensor will be placed on the chest at the fifth intercostal space. The participant will then rest in the supine position for 10 min to stabilize heart rate and blood pressure. R-R intervals will be recorded under the following conditions: (1) after resting in the supine position for 10 min and (2) after resting in the orthostatic position for 10 min (active standing). The participants’ respiratory rate will be recorded throughout the test.

Heart rate variability will be analyzed through spectral analysis in an autoregressive model. The spectral components will be obtained at low frequency (LF, 0.04–0.15 Hz) and high frequency (HF, 0.15–0.4 Hz) bands in absolute units (ms^2^). Standardized units are calculated as the ratio between LF or HF (absolute units) and the power spectral density, minus the very low frequency component (VLF, 0.003–0.04 Hz) and multiplied by 100. The LF band is modulated by the sympathetic and parasympathetic autonomic nervous system (with sympathetic predominance), the HF band is associated with cardiac vagal control, and the LF/HF ratio is calculated to assess sympathovagal balance [30].

